### Secondary Objectives:

2. To assess the acute effect of ADRB2 activation via intravenous administration of salbutamol (250 µg) on resting energy expenditure, serum markers for lipid- and glucose metabolism and plasma BAT markers.
3. To confirm that the stimulatory effect of I.V. salbutamol (250 µg) on [F]FDG uptake by BAT is not mediated by the ADRB3, by showing that the acute effects of ADRB2 activation by salbutamol is blunted when propranolol (ADRB1/2-blocker) is co-administered.

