#### 4. TREATMENT OF SUBJECTS

This is a randomized double-blind cross-over trial in young healthy men. For all subjects the intervention consists of IV injection of salbutamol in combination with placebo and, as comparator, IV injection of salbutamol in combination with propranolol, in random order. In addition, at both study days all subjects will undergo a low-dose dynamic  $^{18}\text{F}$ -FDG PET/CT scan.

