### 7.3.2 Study days

This study encompasses two study days, both will take place in the LUMC. Subjects will be randomized to decide whether they will receive salbutamol in combination with placebo first (study day A) or salbutamol in combination with propranolol (study day B). All measurements during the two study days are identical. Both study days will be performed in the morning after an overnight fast. This means that subjects are not allowed to drink (except water) and eat from 10 PM the evening before, until arrival in the morning. Furthermore, subjects will be asked:

- not to exercise 48 hours in advance;
- not to drink alcohol 24 hours in advance;
- not to drink tea or coffee 24 hours in advance;
- to eat a standardized meal the evening before (options will be given by the researcher).

An overview of the timeline of the two study days and the involved study procedures is given in figure 4.

[figure not shown]

Figure 4 Study procedures.

After arrival anthropometric measurements (including heart rate and blood pressure) will be determined. An intravenous catheter will be placed and a baseline blood sample will be drawn. This will be followed by a resting energy expenditure (REE) measurement for 30 minutes using indirect calorimetry. Directly after the REE measurement subjects will receive either placebo (study day A) or propranolol (study day B). After 60 minutes, heart rate and blood pressure will be measured again (not shown in figure). Then subjects will be placed in the PET/CT scanner and salbutamol will be administered, directly followed by  $[^{18}\text{F}]\text{FDG}$  insertion. First, a low dose CT scan will be performed, followed by dynamic PET acquisition for 60 minutes. While scanning heart rate and rhythm will continuously be monitored. After PET/CT acquisition a blood sample will be drawn, heart rate and blood pressure will be measured and finally REE will be measured for another 30 minutes.

*Anthropometric measurements*

Shortly after arrival (8:00 AM), anthropometric measurements will be performed (weight, height, waist and hip circumference) and heart rate and blood pressure will be measured.

*Blood sampling*

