Next, in both arms a catheter will be inserted in an antecubital vein, for venous blood sampling and for administration of salbutamol and [ $^{18}\text{F}$ ]FDG tracer later during the study day. At two timepoints fasted blood samples will be collected: at the start of the study day and after PET/CT acquisition. In these samples we will determine markers for lipid metabolism (TC, FFA, TG, HDL-C, LDL-C, lipidomics) and glucose metabolism (glucose, insulin). Blood for these measurements will be collected in SST®II Advance Gel tubes of 8 mL and blood collection tubes containing ethylenediaminetetraacetic acid (EDTA) of 8 mL. In addition, we will measure electrolytes (sodium, potassium) in a heparin-lithium tube of 4 mL.

The heparin-lithium tube will directly be brought to the Department of Clinical Chemistry in the LUMC to quickly obtain information about electrolyte levels. The EDTA tube will after blood collection immediately be put on ice and centrifuged promptly (2,000 g at 4°C, for 10 minutes). The SST®II Advance Gel tubes must coagulate for 30-45 minutes before centrifugation. After centrifugation plasma and serum from both tubes will be divided in separate plastic tubes and frozen (-80°C) until assay. Material of all included patients from the SST®II Advance Gel tubes and EDTA tubes will be collected first and then above research markers will be determined all at once at the Department of Endocrinology of the LUMC. The 'rest material' will be stored in the LUMC Biobank Endocriene Ziekten for later additional analysis. For this material the rules and regulations of the LUMC Biobank Endocriene Ziekten are applicable.

An overview of the blood collection during the screening and the study days is provided in table 3.

Table 3 Blood collection during screening visit and study days

| Timepoint         | Measurement                                                                                                                      | Tubes                                                                                   | Amount                                           |
|-------------------|----------------------------------------------------------------------------------------------------------------------------------|-----------------------------------------------------------------------------------------|--------------------------------------------------|

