| Screening  | TC, TG, FFA,
Lipoproteins,
Glucose, Insulin,
Liver-, kidney-,
Thyroid function,
Electrolytes, Full
blood count | SST®II Advance
Gel tube (3.5 mL)
EDTA tube (4 mL)                                 | 7.5 mL                                           |
| Study days | TC, TG, FFA,
Lipoproteins,
Glucose, Insulin,
Sodium, Potassium,
Lipidomics,
BAT markers
(miRNAs)               | SST®II Advance
Gel tube (8 mL)
EDTA tube (8 mL)
Heparin-lithium
tube (4 mL) | 20 mL per
timepoint

4x20 mL = 80
mL |
|                   |                                                                                                                                  |                                                                                         | 87.5 mL                                   |

*Energy expenditure measurement*

At two time points (after the first blood sample and after [ $^{18}\text{F}$ ]FDG PET/CT scan) resting energy expenditure will be measured for 30 minutes with a respiratory gas analyzer using a ventilated hood system (Vyntus Canopy). The volume of inspired oxygen and exhaled carbon dioxide will be measured every minute. Using previously described formulas resting energy expenditure will be calculated [42].

*Administration of medication*

When the first resting energy expenditure measurement has finished, subjects will receive either placebo or 80 mg propranolol per oral. Propranolol will be completely absorbed after oral administration and reaches peak plasma concentrations after 1-2 hours. Therefore, administration of placebo or propranolol will be followed by an hour of rest. Subjects can bring something for entertainment (i.e. a book, magazine, music, etc.), but will not be left alone without supervision of a sub-investigator or research nurse.

After an hour of rest, the study day will continue. Vital signs will be measured again to check whether heartrate and systolic blood pressure meet the accepted values of <100 beats per minute and <140 mmHg, respectively. Then subjects are placed in supine position within the PET/CT scanner and salbutamol will be administered via an

IV injection over a time course of 5 minutes. Administration of salbutamol is directly followed by the administration of a bolus of [ $^{18}\text{F}$ ]FDG tracer in a dosage of 185 MBq using an injection pump.

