### 9.2 Other study parameters

- Energy expenditure, as measured by indirect calorimetry
  - To compare the effect of salbutamol in combination with placebo with the effect of salbutamol in combination with propranolol paired-sample t-test or Mann-Whitney test will be performed.
- Serum markers for lipid metabolism (triglycerides (TG), total cholesterol (TC), high density lipoprotein cholesterol (HDL-C), low density lipoprotein cholesterol (LDL-C), free fatty acids)
  - To compare the effect of salbutamol in combination with placebo with the effect of salbutamol in combination with propranolol paired-sample t-test or Mann-Whitney test will be performed.
- Lipid pathway analysis (lipidomics)
  - To compare the effect of salbutamol in combination with placebo with the effect of salbutamol in combination with propranolol paired-sample t-test or Mann-Whitney test will be performed, in combination with multiple testing correction via false discovery rate estimation.

- Serum markers for glucose metabolism (glucose, insulin)
  - To compare the effect of salbutamol in combination with placebo with the effect of salbutamol in combination with propranolol paired-sample t-test or Mann-Whitney test will be performed.
- Circulating plasma BAT markers (e.g. microRNAs)
  - To compare the effect of salbutamol in combination with placebo with the effect of salbutamol in combination with propranolol paired-sample t-test or Mann-Whitney test will be performed.

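### Objective 2 asks for the acute effect of salbutamol on energy expenditure and blood markers, but chapter 9 states only the contrast with the propranolol day, which addresses blunting

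*Protocol*

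**What the plan says.** The Secondary Objectives separate two questions. Objective 2 begins "To assess the acute effect of ADRB2 activation via intravenous administration of salbutamol" and names REE, serum lipid and glucose markers and plasma BAT markers. Objective 3 is to show that the effect "is blunted when propranolol (ADRB1/2-blocker) is co-administered". It is framed around FDG uptake, but it is the same kind of question for any marker.

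No day is free of salbutamol. Section 4 describes salbutamol with placebo and, "as comparator, IV injection of salbutamol in combination with propranolol, in random order".

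Unlike the PET parameter, the other parameters are measured before any drug and again after the scan, on both days (section 7.3.2):
- Blood: "At two timepoints fasted blood samples will be collected: at the start of the study day and after PET/CT acquisition".
- REE before drug: "This will be followed by a resting energy expenditure (REE) measurement for 30 minutes using indirect calorimetry". Placebo or propranolol follows directly after it.
- REE after the scan: "finally REE will be measured for another 30 minutes".

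Section 9.2 repeats one sentence for all five groups of parameters: "To compare the effect of salbutamol in combination with placebo with the effect of salbutamol in combination with propranolol paired-sample t-test", with the Mann-Whitney test as alternative. The opening of chapter 9 gives the same contrast as the general rule. Nothing in chapter 9 mentions a pre-drug value, a change from baseline or a within-day test.

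**The concern.** The stated comparison matches the blunting question, not the question in Objective 2. If the plan is followed as written, the report will contain a placebo-day versus propranolol-day difference for each marker and no estimate of how the marker moved after salbutamol. Such a difference could then be read as the salbutamol effect, or a null difference as no effect, and neither reading follows. The values needed for a more direct, though imperfect, estimate are already being collected.

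**Working it through.** **1. What each comparison estimates.** For one marker, let
- S = salbutamol effect,
- T = everything else that changes between the pre-drug and post-scan measurements (time, procedure, continued fasting),
- P = propranolol's own effect on the marker,
- b = share of S that propranolol blocks.

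Expected change on the placebo day: T + S.

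Expected change on the propranolol day: T + P + (1 − b)S.

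Between-day contrast: (T + S) − (T + P + (1 − b)S) = bS − P.

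The expectation is the same whether post values or changes are compared, because with random order the pre-drug values have the same expectation under both conditions. The choice affects precision, not the quantity estimated.

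**2. When the contrast equals S.** This requires bS − P = S. In general that means b = 1 and P = 0, apart from chance cancellation.
- With P = 0 and b = 0, 0.5 and 1, the contrast is 0, 0.5S and S.
- With S = 0, the contrast is −P, so a difference can appear without any salbutamol effect.

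On P, the documents give partial information. Section 6.1 reports that 80 mg propranolol almost completely suppressed BAT activity in clinical PET patients and mentions no salbutamol there. So P = 0 cannot be taken for granted for BAT-related outcomes. For REE and the blood markers the documents give no value of P.

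**3. What the placebo-day change estimates.** It estimates T + S, not S. From section 7.3.2, at least 60 min of rest, 5 min of injection and 60 min of scanning (60 + 5 + 60 = 125 min) separate the end of the first REE from the post-scan measurements. Subjects have fasted since 10 PM. T may therefore differ from zero, and no salbutamol-free day exists to estimate it.

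**4. What the pre-drug value can add to the between-day contrast.** The plan gives no figure here. Let ρ be the correlation between the between-day difference in post values and the between-day difference in pre-drug values. It is an assumption, because no value is in the documents. Take n = 10, five per sequence, and equal pre and post variances. Variance relative to comparing post values only:
- Change score: 2(1 − ρ).
- Baseline adjustment alone: (1 − ρ²)(1 + 1/(n − 3)) = (1 − ρ²) × 8/7.
- Baseline and period fitted: (1 − ρ²)(1 + 1/(n − 4)) = (1 − ρ²) × 7/6.

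| ρ | change score | baseline only | baseline and period |
|---|---|---|---|
| 0.3 | 1.40 | 1.04 | 1.06 |
| 0.5 | 1.00 | 0.86 | 0.875 |
| 0.7 | 0.60 | 0.58 | 0.595 |
| 0.8 | 0.40 | 0.41 | 0.42 |

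Simulation of the last column agrees: about 1.06 to 1.08, 0.87, 0.59 and 0.42. Residual degrees of freedom are 9 for the paired t-test, 8 with baseline and 7 with baseline and period.

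**The case against.** **The word effect may already mean change from baseline.** This is a fair reading for parameters measured twice a day. A reader might infer that the plan discards the pre-drug values or has chosen post-only values. The text does not support that: it is silent. But by step 1, a difference of changes still estimates bS − P, so Objective 2 still has no analysis.

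**Change scores, covariates and period terms belong in a SAP.** This stands for the modelling detail. It does not cover the mismatch, because chapter 9 points to specific statistics for each parameter and 9.2 then fixes one comparison for each.

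**The blocked day is the intended reference.** Objective 2 speaks of ADRB2 activation via salbutamol, section 6.1 gives propranolol the role of reversing it, and section 3.4 expects propranolol-day BAT uptake to resemble the thermoneutral state. So the contrast is not unrelated to Objective 2. But section 3.4 states that premise for BAT glucose uptake only. The protocol does not extend it to REE, lipids, glucose or microRNAs, and full blockade is what Objective 3 sets out to examine.

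**The pre/post change is no cleaner.** This also stands. The between-day contrast is randomised and cancels T, and the placebo-day change does not. It would be tempting to say that the data can answer Objective 2 for salbutamol itself. They cannot do so without assuming that T is negligible.

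**Propranolol's own effect on REE or lipolysis is undocumented.** Correct. It is an unverified condition here, not an established bias.

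**Conclusion.** The concern holds as a mismatch between a stated objective and the stated analysis. Chapter 9 addresses blunting for every secondary parameter and gives Objective 2 no analysis of its own. The contrast can stand in for the salbutamol effect only under complete blockade and no effect of propranolol on the marker, and the protocol does not establish either for these markers.

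The direction and size of any misreading cannot be given, because S, b, P and T are unknown. The precision point is secondary and conditional. A reader might take 1 − ρ² as the gain from baseline adjustment, at a cost of one degree of freedom. With 10 subjects that ignores the cost of estimating the slope, and fitting period as well costs two. With both fitted there is no gain at ρ = 0.3, little at 0.5, and a useful gain only well above 0.5.

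The contrast itself is sound as a test of blunting, and neither the primary parameter nor the sample size is affected by this point.

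**What to change.** In section 9.2, state two analyses for each parameter.

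(a) For Objective 2: the mean post-minus-pre change on the salbutamol plus placebo day with a 95% CI, labelled as uncontrolled for time, procedure and fasting. Show the propranolol-day change alongside it. Limit the Objective 2 conclusion accordingly, or reword the objective.

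(b) For blunting: the paired between-day contrast, named as such, with a statement of how the same-day pre-drug value is used (change score or baseline adjustment) and whether period is fitted.

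This is a wording change and needs no new measurements. The costs are that (a) has no time control and that baseline adjustment in (b) uses one degree of freedom, or two if period is also fitted (7 instead of 9). Choose between change score and adjustment before unblinding, since which is more precise depends on a correlation not yet known.

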### 3.4 Sample size calculation

For this study the main outcome parameter is net glucose uptake by BAT after administration of salbutamol, as measured by dynamic  $^{18}\text{F}$ -FDG PET-CT scan.

Our sample size calculation is based on the results recently published by Blondin et al.[1] and Orava et al. [25]. Blondin et al. showed net glucose uptake by BAT as measured by dynamic  $^{18}\text{F}$ -FDG PET/CT after administration of the maximal allowable dose mirabegron (200 mg) of  $22 \pm 14$  nmol/g/min. We expect the effect of salbutamol on glucose uptake by BAT to be at least as big as the effect of the maximal allowable dose mirabegron. Orava et al. [25] showed net glucose uptake by BAT in thermoneutral condition of  $9 \pm 4$  nmol/g/min. Therefore, we predict the net glucose uptake of salbutamol in combination with propranolol to be comparable to the net glucose uptake by BAT in thermoneutral condition. Thus, we consider a difference in net glucose uptake by BAT of  $+13$  nmol/g/min after salbutamol administration as clinically relevant, with a SD of 10,  $\alpha = 0.01$ ,  $\beta = 80\%$ . Based on these parameters we need 10 subjects (<http://biomath.info/power/prt.htm>; based on Snedecor & Cochran, Statistical methods 7th edition).

In case a subject is withdrawn from the study before finishing all measurements, the investigator will try finding a replacement to maintain the initial population size.

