## 9. STATISTICAL ANALYSIS

In general, for differences between the effect of salbutamol in combination with placebo, and salbutamol in combination with propranolol either paired t-tests or Wilcoxon signed-rank tests will be used. Statistical analysis will be performed in close collaboration with our local Medical Statistics Department. More specific information on the statistics to be used for the different study parameters can be found below.

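### Section 9.2 prescribes false discovery rate correction for lipidomics but only the plain two-condition test for the plasma BAT markers, whose number is left open

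*Protocol*

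**What the plan says.** Section 9 of the Protocol opens with a general rule that "either paired t-tests or Wilcoxon signed-rank tests will be used", and says that details for each parameter follow. Section 9.2 then goes through the secondary parameters. Each entry repeats one comparison, ending "salbutamol in combination with propranolol paired-sample t-test or Mann-Whitney test will be performed".

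The lipidomics entry continues: "in combination with multiple testing correction via false discovery rate estimation". No level for the false discovery rate is given. The entry for "Circulating plasma BAT markers (e.g. microRNAs" ends after the test. Nothing else in section 9 gives a multiplicity rule.

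The BAT markers are part of secondary objective 2, which covers "serum markers for lipid- and glucose metabolism and plasma BAT markers". In Table 3 (section 7.3.2) they appear as "BAT markers (miRNAs"), an item separate from lipidomics. The Protocol gives neither a list nor a number of them.

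**The concern.** Two entries in section 9.2 may each hold many molecular measurements: lipidomics and the plasma BAT markers. The Protocol recognises the multiple-testing problem for the first and not for the second, and gives no reason for the difference. The lipid entry (five named markers) and the glucose entry (two) also carry no correction, but there the reader can count the tests. The BAT-marker family is given by example and in the plural, so it can grow after the data are seen.

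What is at stake is one part of secondary objective 2. With ten subjects and an open set of markers, a few that differ between the two days by chance could be presented as responding to ADRB2 stimulation.

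**Working it through.** **Inputs**

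- Number of subjects: 10 (section 3.4).
- Test: paired, comparing salbutamol plus placebo with salbutamol plus propranolol (sections 9 and 9.2). Two-sided testing is assumed, because the Protocol does not state sidedness.
- Number of markers m: not stated, so a range is used.
- Significance level: none is stated for the secondary parameters. The only alpha in the Protocol is 0.01, for the sample size of the main outcome. Both 0.05 and 0.01 are shown.
- Correlation between markers: not stated. 0 and 0.5 are shown.

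**The plan's own figure**

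No figure is given for the BAT markers. The only computed figure is the sample size. Section 3.4 takes a difference of 13 "after salbutamol administration as clinically relevant, with a SD of 10", alpha 0.01 and 80% power, and concludes "Based on these parameters we need 10 subjects". For a paired design, n = (t_alpha + t_beta)² × (SD/difference)², with (10/13)² = 0.592. Iterated on the degrees of freedom with two-sided alpha, this gives 10.07, which matches the stated 10. So n = 10 is used below.

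**Uncorrected testing of m null markers, independent**

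Expected false hits = m × alpha. Chance of at least one = 1 − (1 − alpha)^m.

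| m | Expected, 0.05 | At least one, 0.05 | Expected, 0.01 | At least one, 0.01 |
|---|---|---|---|---|
| 1 | 0.05 | 5% | 0.01 | 1% |
| 5 | 0.25 | 1 − 0.95^5 = 23% | 0.05 | 1 − 0.99^5 = 5% |
| 10 | 0.5 | 40% | 0.1 | 10% |
| 50 | 2.5 | 92% | 0.5 | 39% |
| 100 | 5 | 99% | 1 | 63% |

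**Effect of correlation, and of the correction**

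This was simulated: 3000 runs of m paired t-tests with n = 10, no true differences, level 0.05, and Benjamini-Hochberg at q = 0.05.

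| m | Correlation | At least one false hit, uncorrected | At least one, Benjamini-Hochberg |
|---|---|---|---|
| 10 | 0 | 41% | 4.8% |
| 10 | 0.5 | 31% | 4.0% |
| 50 | 0 | 92% | 4.9% |
| 50 | 0.5 | 66% | 4.3% |
| 200 | 0 | 100% | 5.1% |
| 200 | 0.5 | 91% | 4.5% |

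The independent, uncorrected rows only confirm the formula. The added information is in the correlated rows and the last column.

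**A limit on the correction at n = 10**

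The smallest two-sided p-value of the signed-rank test with ten pairs is 2/2^10 = 0.00195. Under Benjamini-Hochberg, a lone marker must have p ≤ q/m. With q = 0.05 this needs m ≤ 0.05/0.00195 = 25.6, so m of 25 or fewer. The limit applies to the signed-rank test named at the start of section 9; the paired t-test has no such floor.

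**The case against.** The strongest reply is that the Protocol is silent rather than wrong. A reader might infer from the contrast with lipidomics that the BAT markers are deliberately to be tested without correction. The text does not say that: the entry names a test and stops. Multiplicity for secondary markers is also often settled in a statistical analysis plan, which may exist here. That stands as to wording. It does not remove the point, because section 9 presents its subsections as the place where the statistics for each parameter are specified, and section 9.2 does deal with multiplicity there, for one family only.

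It can also be said that no microRNA panel or profile is described. Lipidomics is an omics screen, whereas the others are called markers, and the lipid and glucose markers have no correction either. This is a coherent reading, and with one or two pre-chosen candidates the problem is negligible. But the Protocol does not say that the set is small, and unlike the lipid and glucose entries it does not name its members.

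Finally, the size depends on assumptions. At 0.01, or with correlated markers, the risk is clearly lower than at 0.05 with independence. That is correct, and it is why a range is given.

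**Conclusion.** The point holds as an inconsistency of low severity. The Protocol corrects one multi-marker family and gives another, open-ended one only the plain test. Depending on m, the chance of at least one false hit at 0.05 runs from 5% (one marker) through 23% (five) and 40% (ten) to 92% (fifty) with independence. With correlation 0.5 it is about 31% for ten and 66% for fifty. At 0.01 with independence it is about 5% for five, 10% for ten and 63% for a hundred. These figures assume that none of the markers truly differs between the two days; m, the level and the correlation are all assumptions.

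A reader might go further and infer that chance hits would be reported as BAT markers. The documents do not support this. The comparison asks whether a marker differs between salbutamol with placebo and salbutamol with propranolol; it does not establish that a molecule is a marker of BAT. Nor does the Protocol have a rule on how significant markers are reported. What can be said is that chance findings could be reported as responses to ADRB2 stimulation. The primary analysis of glucose uptake by BAT is not affected.

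**What to change.** In section 9.2, extend the lipidomics correction to the BAT-marker entry:

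- Apply Benjamini-Hochberg with a stated q across all plasma BAT markers tested, not only the microRNAs.
- Fix the list of markers, or at least their number, before unblinding.
- Report the number tested, with raw and adjusted p-values side by side.

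The cost is a sentence or two of text and trivial analysis work, with no new data or visits. If only one marker is tested, the correction changes nothing. The downside is that fewer markers will be called significant. With the signed-rank test and ten subjects, a single true responder cannot pass at q = 0.05 once more than 25 markers are tested, which favours a short list chosen in advance.
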